**Interventions**

***Multimedia pain management education***

Eligible participants in this group will receive multimedia PME in seven weeks. The modules of this education will consist of definition of chronic pain and the psychological factors affecting pain experience (the first session), appropriate physical exercises for chronic LBP (the second session), effective communication skills (the third session), assertiveness skills (the fourth session), stress management skills (the fifth session), positive thinking skills (the sixth session), and anger management skills (the seventh session). Educational materials will be developed based on the existing literature on chronic pain management ([Dobson, 2010](#_ENREF_7); [Dobson & Dozois, 2010](#_ENREF_8)). Educational modules will consist of textual and audiovisual data. Each week during the study intervention, one of the CDs will be provided to participants and they will be asked to watch it at home in forty minutes. After watching two educational CDs, an FTF session will be held for answering the questions of participants in the multimedia group. Moreover, a WhatsApp group will be formed where the third author answered patients’ questions and encouraged them for using educational materials.

***Face-to-face pain management education***

For participants in the FTF group, the third author will provide the same educational materials as multimedia group through the lecture, question-and-answering, and PowerPoint presentation methods in seven weekly sessions, each last 60–90 minutes. Participants in this group will receive educations in the form of small 8–10-person groups.

***Wait-list control group***

Participants in the control group will receive routine care services. Participants in this group will be asked not to participate in any other educational programs during the study and will be provided with the multimedia educational CDs at the end of the study. All participants in all groups will complete the study instruments before, immediately after, and one month after the study intervention.

**Safety considerations**

All methods will be carried out in accordance with the Declaration of Helsinki and relevant guidelines and regulations. All participants will be informed about the study aim and ensured that participation in and withdrawal from the study would be voluntary. Written informed consent will be obtained from all of them. Study instruments will be anonymous and be labeled with numerical codes. At the end of the study, educational CDs will be provided to participants in the control group and their questions will be answered.

**Follow-up**

Participants in the multimedia PME group will receive PME through watching seven educational CDs at home and their counterparts in the FTF PME group receive the same educations in seven weekly FTF educational sessions.

**Data management and statistical analysis**

Data collection instruments will be a demographic and clinical characteristics questionnaire, a numerical rating scale for pain intensity, and the Pain Catastrophizing Scale. The items of the demographic and clinical characteristics questionnaire will be on age, gender, marital status, educational level, occupation, duration of LBP, and type of LBP treatments.

***Primary outcome: Pain intensity***

The numerical rating scale (NRS) will be used to assess the average intensity of pain during the last 2 weeks. It is an eleven-point scale with 0 (“No pain”) on the one end and 10 (“Worst possible pain”) on the other. Respondents are asked to circle a point in the 0–10 range to show their pain intensity. This scale was developed by Jensen et al. and has been used in different studies for assessing different types of pain among different populations ([Jensen, Karoly, & Braver, 1986](#_ENREF_14)). Minimal detectable change (MDC) for this scale in patients with specific back pain was calculated as 1.77 by Hasse & Kladny ([Haase & Kladny, 2021](#_ENREF_11)).

***Secondary outcome: Pain catastrophizing***

Previous studies showed that patients with improvement in pain intensity also experienced improvement in pain catastrophizing ([Shaygan, Böger, & Kröner-Herwig, 2019](#_ENREF_22)). Therefore, pain catastrophizing will be considered as the secondary outcome in the present study and assessed using the Pain Catastrophizing Scale. The PCS was developed in 1995 by Sullivan et al. and contains thirteen items on the frequency of pain-related thoughts in three main dimensions, namely rumination (4 items), magnification (3 items), and helplessness (6 items). Items are scored on a five-point scale from 0 (“Never”) to 4 (“Always”). PCS total scores range from 0-52. The higher scores show that the client experiences more pain catastrophizing ([Sullivan, Bishop, & Pivik, 1995](#_ENREF_25)). A former study reported that the Cronbach’s alpha values of the scale and its rumination, magnification, and helplessness dimensions were 0.94, 0.98, 0.78, and 0.78, respectively ([Chibnall & Tait, 2005](#_ENREF_4)). A study in Iran also reported that the Cronbach’s alpha of the questionnaire was 0.86 and the coefficient of correlation between the scores of this questionnaire and the scores of the short form of the Beck Depression Inventory was 0.46 ([Davoudi, Zargar, Mozaffaripour, Nargesi, & Molah, 2012](#_ENREF_6)). The MDC for this scale was adopted from Sharma et al. (2018) study which was 6.98 ([Sharma, Thibault, Abbott, & Jensen, 2018](#_ENREF_21)).

**Data analysis**:

Data will be entered into the SPSS software (v. 22.0) and analyzed at a significance level of less than 0.05. The Kolmogorov-Smirnov test will be performed to test the normality of the study data. Data will be described via the measures of descriptive statistics, namely mean, standard deviation, absolute frequency, and relative frequency. Groups will be compared with each other using the Chi-square test (for categorical variables) or the one-way analysis of variance (for numerical variables). To analyze treatment effects, a repeated-measures multivariate analysis of variance (MANOVA) with Tukey’s post hoc test will be performed. Effect sizes will be reported where appropriate and calculated by Partial ɳ^2^. The following are small, medium, and large effects for ɳ^2^, respectively: .01, .06, and .14 ([Stevens, 1996](#_ENREF_24)). Clinical outcome (MDC) for pain intensity and catastrophizing will be also reported. MDC means that the participants with a change score smaller or equal to the MDC have a chance of more than 95% that no real change has occurred.

The regression model used in the present study will be Generalized Estimating Equations (GEE). GEE procedure extends the generalized linear model to allow for analysis of repeated measurements or other correlated observations. To do so, after choosing the “Generalized estimating equations”, in the “*Repeated”* tab, the time will be entered to the within-subject variables box, in the “*Type of mode”*, the linear icon will be chosen in the scale response box, and in the “*Response”* tab, the pain intensity/pain catastrophizing will be entered in the dependent menu. In the “*Predictors”* menu, we will enter the predictors “group, pain catastrophy and time” for pain intensity and “group, pain intensity and time” as the predictors for pain catastrophy.

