Some previous studies evaluated the effects of technology-based pain management programs ([Garg, Garg, Turin, & Chowdhury, 2016](#_ENREF_10); [Vugts, Joosen, van der Geer, Zedlitz, & Vrijhoef, 2018](#_ENREF_31)). However, most of them were web-based programs ([Garg et al., 2016](#_ENREF_10); [Nevedal, Wang, Oberleitner, Schwartz, & Williams, 2013](#_ENREF_18)), single-center, and non-controlled ([Bérubé et al., 2021](#_ENREF_3); [Shearer et al., 2016](#_ENREF_23)). Moreover, there are limited comparative studies into the effects of FTF and multimedia pain management programs ([Suman, Schaafsma, Bamarni, Van Tulder, & Anema, 2017](#_ENREF_26); [Suman et al., 2018](#_ENREF_27)). On the other hand, the results of the existing studies in this area may not be generalizable to different context because the effects of psychological factors on chronic pain largely depend on patients’ sociocultural background ([Kovacs et al., 2012](#_ENREF_15)). Nonetheless, most previous studies into pain catastrophizing and pain were conducted in northern European countries and Anglo-Saxon cultures ([Hirsh, George, Riley III, & Robinson, 2007](#_ENREF_13); [Moix, Kovacs, Martín, Plana, & Royuela, 2011](#_ENREF_17)). There is limited information in this area in the culture of Asian countries, particularly in Iran. Therefore, studies in different contexts and cultures are needed to provide more reliable results regarding the effects of multimedia pain management program on chronic LBP and pain catastrophizing ([Kovacs et al., 2012](#_ENREF_15)). All these gaps highlight the necessity of conducting further studies into pain catastrophizing among patients with chronic LBP and the comparative effects of face-to-face and multimedia treatments in this area. The present study was designed and conducted to reduce these gaps. The aim of the current study was to compare the effects of multimedia and face to face (FTF) pain management education (PME) on pain intensity and pain catastrophizing among patients with chronic LBP. The hypothesis of the present study was that patients with chronic back pain who receive FTF and multimedia PME will show significant decrease in pain intensity and pain catastrophizing, assessed immediately after program and at 1-month follow-up.

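### Two unranked models test the effect of group on pain at 0.05, and no deciding contrast or visit is named

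*Protocol*

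**What the plan says.** All of this is in the protocol.

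- **Level.** Under Data analysis, the data will be "analyzed at a significance level of less than 0.05".
- **First model.** The same section says: "To analyze treatment effects, a repeated-measures multivariate analysis of variance (MANOVA) with" Tukey's post hoc test.
- **Second model.** Its next paragraph says: "The regression model used in the present study will be Generalized Estimating Equations (GEE"). The predictors of pain intensity are "group, pain catastrophy and time". No group-by-time term is listed.
- **Primary outcome.** The heading is "Primary outcome: Pain intensity". The text below it describes the 0–10 numerical rating scale (NRS) but names no time point.
- **Hypothesis.** The end of the Rationale section says that patients in the two education groups "will show significant decrease in pain intensity and pain catastrophizing, assessed immediately after program and at 1-month follow-up". The two visits have equal standing.
- **Objectives.** Change in mean pain score is to be compared between groups, without naming a visit.

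No section ranks the two models or says which result decides if they differ.

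**The concern.** Group is a term in both models, and both are fitted to the same primary outcome at the same level. A significant group result from either could be reported as an effect on pain. If either is enough, the chance of a false claim is larger than 5%. If they conflict, the reader has no rule set in advance.

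The conflict is not remote, because the models estimate different things. The MANOVA group-by-time test asks whether the arms change differently. The GEE as listed gives one group coefficient across before, immediately after and one month after. It therefore includes the baseline visit, at which randomised arms should not differ. It also adjusts for catastrophizing at the same visit, which is the trial's secondary outcome and may itself respond to the education.

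This is more than detail left to a statistical analysis plan. The section fixes the analysis down to the software menus and predictor boxes, and what it fixes is two unranked analyses.

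**Working it through.** **Inputs from the protocol.** Level 0.05; three arms; three assessments; 90 patients in all (Design summary), that is 30 per arm, or 36 per arm (Study design). The predictors of the GEE are as listed.

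**Assumed, because the protocol does not give them.** Correlation of a measure between visits 0.3–0.7; correlation of pain with catastrophizing 0.3–0.5; independence working correlation with robust Wald test for the GEE.

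**Step 1. The stated level.** One test at 0.05 has error 0.05. In simulations with no true effect (4,000 trials per setting), the MANOVA group-by-time test alone was significant in 4.7–5.7%. Used alone, it delivers the stated level.

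**Step 2. Either model may carry the claim.**
- Two independent tests: 1 − (1 − 0.05)² = 0.0975. Upper bound: 0.05 + 0.05 = 0.10.
- Simulated: 10.3–11.9%.
- The simulated figure passes the bound because the GEE robust Wald test alone ran at 5.8–7.2% with 30–36 per arm. With those rates, 1 − 0.95 × 0.942 = 0.105 and 1 − 0.95 × 0.928 = 0.118, close to the simulated range. So most of the excess over 5% comes from having two nearly unrelated tests, and a smaller part from the small-sample behaviour of one of them.

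**Step 3. A real effect.** Assume a benefit of 0.7 SD in both education arms, on both outcomes, at both follow-up visits. The between-visit correlation is here 0.5–0.7, with 3,000 trials per setting.
- Average difference over three visits, baseline included: (0 + 0.7 + 0.7) / 3 = 0.47 SD.
- Catastrophizing moves in parallel, so adjusting for it removes roughly its correlation with pain times that difference. What remains is about 0.47 × (1 − 0.3) = 0.33 SD, or 0.47 × (1 − 0.5) = 0.23 SD.
- Simulated: MANOVA interaction significant in 82–99% of trials, GEE group term in 22–44%, and opposite verdicts in 55–76%.

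**Step 4. The proposed analysis.** A baseline-adjusted test of the arms at one month, under the same 0.7 SD effect, had about 90–99% power, against 28–33% for the GEE group term in that separate run. The gain over the MANOVA interaction is modest. The larger gains are over the GEE and in having one clear answer.

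**The case against.** The strongest reply is that the phrase about analysing treatment effects is attached to the MANOVA alone. The GEE is introduced separately as a regression model, with pain and catastrophizing each predicting the other, and it can be read as an analysis of predictors. An analysis plan that is not shown may say so. On that reading the MANOVA decides and 5% holds. This is a fair reading, but the protocol does not state it, and group stands in the GEE as a predictor of pain.

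It is also true that 0.05 is given as a level for the analyses and never as an overall rate. The 10–12% therefore rests on an either-model rule that the protocol neither states nor excludes.

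Three stronger readings are tempting, and the document does not support them:

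- **A separate 0.05 test at each follow-up visit.** A reader might infer this from the two-visit hypothesis. Both models take all assessments together, and no per-visit test is planned. A false-positive rate of about 8–10% for two visit tests would apply only if such tests were added and success at either were enough. The hypothesis joins the visits with *and*. If both had to succeed, two visits would not inflate the error.
- **Pooling catastrophizing with pain in one error rate.** The protocol already ranks catastrophizing as secondary.
- **The immediate visit as a defect in itself.** The NRS asks for "average intensity of pain during the last 2 weeks", so at that visit it looks back over the end of a seven-week programme. That is a reason to weigh when choosing a visit. It has no bearing on false-positive control, and an end-of-programme assessment is a legitimate target.

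**Conclusion.** The point holds in this form: the protocol specifies two unranked models for the effect of group on the primary outcome, each at 0.05, and names no deciding contrast or visit.

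If either model may support a claim, the false-positive rate is about 10–12% rather than 5%, with 30–36 per arm and the correlations assumed above. If there is a real effect of the assumed size, disagreement between the models is the usual result. The disagreement figure depends on the 0.7 SD effect and on catastrophizing improving together with pain. Neither comes from the protocol.

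It would go too far to say that the 5% level fails whatever rule is used. Taken alone as the deciding test, the MANOVA interaction keeps it.

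**What to change.** In Data analysis, name one primary analysis of NRS pain: a longitudinal model of the follow-up scores with arm, visit, arm-by-visit and baseline NRS. Test the Tukey-adjusted contrasts between the three arms at one pre-specified follow-up visit at 0.05. One month is a reasonable choice and avoids the recall overlap with the programme, but the sponsor may choose the other visit.

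Label as supportive, with estimates and 95% confidence intervals, the MANOVA, the GEE that includes catastrophizing, the other visit and catastrophizing as an outcome. State that the GEE group coefficient is not read as the treatment effect.

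Align the hypothesis in the Rationale section and the primary outcome text with the chosen visit.

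Testing the two existing models at 0.025 each would also cap the error (1 − 0.975² = 0.0494 if independent). It would leave two different questions standing as one primary claim, so it is the weaker remedy.

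The cost is a few sentences in three sections, with no extra patients, visits or data. The downside is that the other visit or model can no longer carry the primary claim alone.

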**Objectives:**

- Determining the demographic variables of participants
- Determining and comparing the mean score of pain intensity within the interventions and control groups, before, immediately and one month after intervention
- Comparing the changes of the mean score of pain intensity between the intervention and control groups
- Determining and comparing the mean score of pain catastrophizing within the interventions and control groups, before, immediately and one month and after intervention
- Comparing the changes of the mean score of pain catastrophizing between the interventions and control groups

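### The GEE as listed has no group-by-time or baseline term, and no pairwise comparison of change is specified, although the objective is to compare changes between groups

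*Protocol*

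**What the plan says.** Among the objectives in the Protocol is "Comparing the changes of the mean score of pain intensity between the intervention and control groups"; catastrophizing has a parallel objective. Both outcomes are measured once before the intervention and twice after it (immediately and at one month).

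The Data analysis section describes two analyses. For treatment effects, "a repeated-measures multivariate analysis of variance (MANOVA) with Tukey’s post hoc test will be performed". It does not say which term (group, time or group-by-time) is the treatment test, or whether Tukey's test is applied at each visit or overall.

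The section then describes a GEE almost menu by menu: "the time will be entered to the within-subject variables box", and the predictors for pain intensity are listed as "group, pain catastrophy and time". The model for the secondary outcome mirrors this, with "group, pain intensity and time” as the predictors for pain catastrophy". Neither list contains a group-by-time term or the baseline value of the outcome.

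**The concern.** In a model with group and time but no interaction, the group coefficient is one constant difference across all visits. One of those three visits precedes treatment. The coefficient is therefore not a difference in change, and it mixes a visit with no expected effect with two visits that may have one. Chance imbalance at baseline also goes straight into the estimate.

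The named follow-up, Tukey's test, does not repair this. As usually run on a between-subject factor after a repeated-measures analysis, it compares group means averaged over the visits.

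What is at stake is the between-arm inference on the primary outcome, including multimedia against face-to-face, in a trial whose size is given as 90 in the summary and 36 per group (108) under Study design. A three-arm omnibus test alone would not show which arms differ.

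**Working it through.** **Inputs.** From the Protocol: three visits (one pre, two post); 36 per group; 20% attrition, so 36 × 0.8 = 28.8, about 29 per arm; minimal detectable change for pain intensity 1.77, used here only as an illustrative effect. The Protocol gives no SD, between-visit correlation r, target difference or power, so there is no figure of its own to reproduce. Assumed: SD 2, r = 0.3 to 0.7, equal correlation between visits, two-sided 0.05.

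**Dilution, without the catastrophizing term.** The expected between-group differences at the three visits are 0, d and d.
- Visit-pooled difference: (0 + d + d)/3 = 2d/3. With d = 1.77 this is 1.18.
- If the effect halves by one month: (1.77 + 0.885)/3 = 0.885, against a post-visit average of 1.3275. Again one third is lost.

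A GEE fitted to simulated data (4,000 per arm, SD 2, r = 0.5, true effect −1.77 at both post visits) agreed. With group and time only, the group coefficients were −1.19 and −1.20 under both independence and exchangeable working correlation. With group-by-time added, the interaction terms were −1.69 to −1.75.

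**The GEE as written.** In the same simulation, catastrophizing was also improved by 6.98 (the scale's minimal detectable change in the Protocol, again only an assumption). Entering it as a concurrent predictor moved the group coefficients to between −0.47 and −0.53. That value depends on the assumed link between the two outcomes. It shows only that one third does not describe the full model.

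**Efficiency.** The variance factors, in units of SD², are:
- mean of three visits: (1 + 2r)/3
- one post visit, adjusted for baseline: 1 − r²
- mean of two post visits, adjusted for baseline: (1 + r)/2 − r²
- mean of two post visits minus baseline: (1 + r)/2 + 1 − 2r

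The efficiency of the pooled contrast relative to the baseline-adjusted post-visit mean is (4/9) × [(1 + r)/2 − r²] / [(1 + 2r)/3] = (2/3)(1 − r). This gives 0.467, 0.333 and 0.200 for r = 0.3, 0.5 and 0.7.

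**Power at 29 per arm, SD 2, d = 1.0.** SE = 2 × √(factor) × √(2/29), z = effect/SE, and power = Φ(z − 1.96) unadjusted. With a Tukey critical value for three groups of about 2.39, power = Φ(z − 2.39). At r = 0.5:

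| Contrast | Effect | SE | z | Unadjusted | Tukey |
|---|---|---|---|---|---|
| Pooled over three visits | 0.667 | 0.429 | 1.55 | 34% | 20% |
| One post visit, baseline-adjusted | 1.0 | 0.455 | 2.20 | 59% | 42% |
| Post-visit mean, baseline-adjusted | 1.0 | 0.371 | 2.69 | 77% | 62% |
| Post-visit mean minus baseline | 1.0 | 0.455 | 2.20 | 59% | 42% |

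Unadjusted power for the first three rows is 41%, 51% and 72% at r = 0.3, and 29%, 76% and 89% at r = 0.7.

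**At a larger effect.** With d = 1.77, SD 2, r = 0.5 and 30 per arm, unadjusted power is 80% pooled and 98% for change. The loss narrows when the effect is large.

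**The case against.** The strongest reply is that the Protocol assigns treatment effects to the repeated-measures MANOVA, not to the GEE. With group between and time within subjects, that analysis ordinarily produces a group-by-time test, which is a test of differential change and is not diluted. A reader might infer that change between groups goes untested. The document does not support that: it leaves the term unnamed but does not exclude it. What survives is narrower: the test is not designated, it is omnibus, and no pairwise comparison of change follows it.

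Three further limits stand.
- The absence of an interaction is read from the predictor list. SPSS sets model terms in a separate step that the Protocol does not describe, and a statistical analysis plan may exist. The interaction is unstated, not ruled out.
- That Tukey's test averages over visits is usual software behaviour, not Protocol text.
- A reader might infer that the MANOVA pools pain intensity and catastrophizing in one test. No list of dependent variables is given, and the term can equally mean the multivariate approach to repeated measures of one outcome.

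It can also be said that baseline adjustment in preference to group-by-time is a matter of taste. Both do target change. Baseline adjustment has the smaller variance under the assumed model, since the two factors for the post-visit mean differ by (1 − r)². Unadjusted change is not always more powerful than the pooled contrast: their efficiency ratio is 2(1 − r)/(1 + 2r), which reaches 1 at r = 0.25.

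**Conclusion.** The point holds as a mismatch between objective and specification. The GEE as listed does not estimate a between-group difference in change, and the Protocol names neither a group-by-time treatment test nor a pairwise comparison of change.

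The one-third dilution is exact for a group-plus-time contrast with no expected baseline difference, measured against the post-visit average. It should not be read as the size of the distortion in the GEE as written, which also conditions on concurrent catastrophizing.

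The power figures rest on assumed SD, correlation and effect. They indicate a worthwhile loss against a baseline-adjusted analysis over r = 0.3 to 0.7, not a forecast for this trial.

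**What to change.** State one primary analysis of pain intensity that targets change. Either of these would do:
- a GEE or linear mixed model of the two post visits with group, visit, group-by-visit and baseline pain intensity; or
- a model of all three visits with group, time and group-by-time.

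Define the primary contrast in advance as either the average of the two post visits or one named visit. Make the Tukey-adjusted pairwise comparisons on that contrast, and report differences with 95% confidence intervals. Analyse catastrophizing separately in the same way, as secondary.

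The cost is a few sentences in the Data analysis section, with the same data and software. The downside is that the contrast must be chosen now, and that a single visit gives up power against the post-visit average (59% against 77% unadjusted in the r = 0.5 example). Of the two models, the baseline-adjusted one is the more efficient under the assumptions above.
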